### Recruitment

All individuals aged 18 years and older who have liver function tests and full blood count requested by a community-based health worker and performed at St Vincent’s Pathology between August 1, 2023, and July 31, 2024, will be recruited. There will be no active recruitment of participants for this study.

This study is an evaluation of a health system–wide introduction of routine reporting of APRI calculation, information on liver cirrhosis, and a web link through St Vincent’s Pathology to improve the quality of care for people with liver disease; therefore, no individuals will individually consent to participate. No personally identifying information will be collected and all data supplied to the research team will be deidentified by St Vincent’s Pathology and transient elastography booking and reporting teams, respectively. Variables including 10-year age category, sex, and postcode will be collected as part of the study but will not allow identification of individuals, as they are broad categories expected to contain more than 1000 persons per strata per month during the study period.

The exclusion criteria of this study include children aged 18 years or younger and blood tests performed during a hospital inpatient stay, or requested by hospital outpatient service, defined by St Vincent’s Pathology records (blood collection site).

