### Hypothesis

Automated calculation and reporting of APRI and FIB-4 on routinely ordered blood tests and provision of information about liver cirrhosis, including a link for transient elastography referral, will increase the diagnosis of liver cirrhosis and linkage to specialist care.

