### Definitions

#### Comparator Group (Standard of Care)

Currently, APRI and FIB-4 scores are not routinely reported anywhere in Australia. Prior to the intervention, blood tests will be reported per standard of care. APRI and FIB-4 scores will be calculated automatically by the pathology service from the start of the study but will not be reported to ordering clinicians until the intervention period. FibroScans are requested through a paper-based referral form by general practitioners or specialists, which is then faxed to the hospital for triage and booking.

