### Statistical Analysis Plan

#### Outcome Measures

Data will be analyzed per test event and per individual tested.

Primary outcomes of this study include the number of APRI and FIB-4 scores calculated on blood test events conducted during the study period, overall and per month; the number (proportion) of APRI scores that are greater than 1.0 and FIB-4 scores that are greater than 2.67; number of FibroScan referrals overall and per month, operationalized as number of completed FibroScan referrals generated online using the recommended St Vincent’s Pathology FibroScan referral link on the request slip, or St Vincent’s Pathology APRI or FIB-4 calculation web page referral form link; number of individuals with an APRI greater than 1.0 or FIB-4 score greater than 2.67 who undergo a FibroScan test at St Vincent’s Hospital Melbourne overall and per month; proportion of individuals with an APRI greater than 1.0 or FIB-4 score greater than 2.67 who undergo a FibroScan test at St Vincent’s Hospital Melbourne; the number of individuals per month who undergo FibroScan at St Vincent’s Hospital Melbourne who have cirrhosis diagnosed (liver stiffness measurement >12.5kPa); the number (proportion) of individuals with an APRI greater than 1.0 or FIB-4 score greater than 2.67 who have cirrhosis confirmed by FibroScan; the number (proportion) of individuals with etiology-specific cirrhosis range FibroScan results that are referred to the specialist liver clinic; and the number (proportion) of individuals with etiology-specific cirrhosis range FibroScan results that attend to the specialist liver clinic appointment.

The secondary outcomes of this study include the number (proportion) of individuals, stratified by age category, sex, and postcode who have elevated APRI greater than 1.0 and FIB-4 score greater than 2.67, attend the FibroScan clinic for further testing, have etiology-specific cirrhosis range FibroScan scores (kPa), and attend a liver specialist clinic appointment.

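### The diagnosis and linkage outcomes are not limited to new cases, and nothing removes or flags people already known to have cirrhosis or already under the liver clinic

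*Protocol article*

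**What the plan says.** All references are to the protocol article.

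- **Claim (Hypothesis).** Automated reporting with information and a referral link "will increase the diagnosis of liver cirrhosis and linkage to specialist care". The Abstract says that monthly diagnosis rates and the proportion linked will be compared between the 6 months before and the 6 months after the intervention.
- **Diagnosis (Outcome Measures).** One primary outcome is "the number of individuals per month who undergo FibroScan at St Vincent’s Hospital Melbourne who have cirrhosis diagnosed (liver stiffness measurement >12.5kPa"). A separate item counts cirrhosis confirmed among people with a raised APRI or FIB-4.
- **Linkage (Outcome Measures).** The two items are the number and proportion of "individuals with etiology-specific cirrhosis range FibroScan results that are referred to the specialist liver clinic" and of "individuals with etiology-specific cirrhosis range FibroScan results that attend to the specialist liver clinic appointment".
- **Who enters (Recruitment).** Included are "All individuals aged 18 years and older who have liver function tests and full blood count requested by a community-based health worker". Excluded, apart from the age limit, are "blood tests performed during a hospital inpatient stay, or requested by hospital outpatient service, defined by St Vincent’s Pathology records (blood collection site").
- **Who is scanned (Comparator Group).** "FibroScans are requested through a paper-based referral form by general practitioners or specialists".
- **What is collected (Exposure Variables Collected).** The list has sex, age category, two postcode-based measures and the liver disease indication on the FibroScan request. It has no field for an earlier cirrhosis-range scan, a recorded cirrhosis diagnosis or current liver-clinic care.

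**The concern.** An increase in diagnosis and linkage means people newly found and newly brought into care. None of the printed outcomes asks for a first cirrhosis-range result, a new referral or a first attendance. A repeat scan in a patient followed for years counts as a diagnosis, and that patient's routine clinic visit can count as linkage.

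If such patients form a material part of the cirrhosis-range scans, the absolute figures overstate what the programme finds. The before-after change in linkage then mixes the effect of the intervention with any change in the mix of known and new patients. A change in mix is plausible because the intervention adds a second referral route, the web form described under Intervention Period.

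A smaller problem sits in the same eligibility text. Both the inclusion and the exclusion turn on who requested the test, but the exclusion is put into practice by where the blood was taken.

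**Working it through.** **1. Can a known case reach the outcomes?** Take a person with established cirrhosis whose general practitioner orders liver tests and a full blood count.
- The inclusion rule is met, because the requester is community-based.
- The hospital exclusion does not apply, because the test is neither inpatient nor requested by a hospital clinic.
- If scanned above 12.5 kPa, the person is counted as diagnosed. If the score was raised, the person is also counted in the raised-score item.
- No listed variable separates this person from a new case.

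The first diagnosis item is not restricted to people with a raised score, so as worded it also takes in specialist-requested scans. The article itself expects known disease among those tested: under Intervention Period, the advice to run a liver disease screen is limited to people whose liver disease has not already been established.

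**2. Requester against collection site.**

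| Requested by | Blood taken at | Inclusion rule | Exclusion as defined by site |
|---|---|---|---|
| Community | Community | in | kept |
| Community | Hospital | in | dropped |
| Hospital clinic | Community | out | not caught |
| Hospital clinic | Hospital | out | dropped |

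The two rules disagree in the middle rows. Neither rule touches the known patient in step 1, so mending this conflict does not solve the main problem.

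**3. Effect on counts.** Let f be the known share of cirrhosis-range scans before the intervention, let R be the true ratio of new cases after to before, and let the number of known cases stay constant.
- Absolute difference in monthly counts: the known cases cancel.
- Observed ratio = f + (1 − f) × R, so observed relative increase = (1 − f) × (R − 1). At f = 50%, half of the relative increase is lost.

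**4. Effect on linkage.** Observed linkage = f × L_known + (1 − f) × L_new. The article gives none of these inputs; every value below is an assumption.

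*Stable share.* L_known = 100% and L_new rises from 40% to 60%, a true change of 20 points. Observed change = (1 − f) × 20 points:
- f = 0%: 20 points
- f = 10%: 18 points
- f = 25%: 15 points
- f = 50%: 10 points (0.5 + 0.5 × 0.4 = 70%, then 0.5 + 0.5 × 0.6 = 80%)

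*Shifting share, no real change.* L_new = 50% in both periods and f falls from 40% to 20%.
- Known patients all count as linked: 0.4 × 1 + 0.6 × 0.5 = 70%, then 0.2 × 1 + 0.8 × 0.5 = 60%. Linkage appears to fall by 10 points.
- Known patients never count as linked: 0.6 × 0.5 = 30%, then 0.8 × 0.5 = 40%. Linkage appears to rise by 10 points.

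In general, with L_new constant, the spurious change is (f_after − f_before) × (L_known − L_new). It is zero if the share does not move.

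**The case against.** **Stronger readings that the article does not support.**
- *That leakage is large.* Sample Size Justification reports about 11,000 people known to the hospital's clinics and 4400 in the community: 11,000 + 4400 = 15,400, and 11,000/15,400 = 71%. A reader might take this as a contamination rate. It is a 2019 count of people known to any clinic, with no mention of cirrhosis or the study's exclusions, so it estimates neither known cirrhosis nor leakage.
- *That known patients are linked by definition.* The outcomes are referral and attendance. A patient already under the clinic may need no new referral and so count as not referred, while attending a routine appointment and so counting as attended. The two linkage items could move in opposite directions.
- *That any effect is diluted.* A stable number of known cases cancels from an absolute difference in counts.
- *That collection site lets hospital-clinic patients in.* Read with the inclusion rule, and with Intervention, which speaks of requests by primary care physicians, a clinic-requested test is already out. What remains is an internal conflict, whose certain casualty is the community patient bled at a hospital site.

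**Points in the plan's favour.** The raised-score item narrows the diagnosis count, and the separate web form identifies referrals generated by the intervention. This is a pilot reported in a condensed article, and first-event rules are often left to a fuller document.

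These points limit the concern but do not remove it. The raised-score item still admits known cases tested in primary care. The web form did not exist before the intervention, so it cannot separate known from new cases in both periods. The eligibility and outcome definitions are not left open: the article prints them, the outcomes under its own Statistical Analysis Plan heading, without a new-case condition.

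**Conclusion.** The point holds in a limited form. Followed as printed, the plan mixes existing cases into outcomes meant to show more diagnosis and more linkage. This rests on the wording of the definitions and on the article's own indications that specialists request scans and that some tested people have known liver disease.

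The absolute diagnosis figures are inflated, and ratios and proportions are attenuated. The linkage contrast can be biased either way, but only if the known share shifts between periods. The size and direction cannot be computed from the document; the 10-point examples rest wholly on assumed shares and linkage rates. The collection-site wording is a secondary inconsistency to reconcile.

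**What to change.** For the before-after comparison:

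1. **Diagnosis:** a first cirrhosis-range FibroScan in a person with no earlier cirrhosis-range result and no recorded cirrhosis diagnosis in the hospital record within a stated look-back. Use the same cirrhosis-range definition in the look-back as in the outcome.
2. **Linkage:** a new referral to, or first attendance at, the liver clinic after that scan, among people not currently under the clinic. Former clinic patients who were never in the cirrhosis range should stay in, since a cirrhosis-range scan in them is a new finding.
3. **Handling:** apply the same rule and look-back length in both periods, and report known cases in a separate row.
4. **Eligibility:** reconcile the two rules under Recruitment by applying the hospital exclusion on the requester field. The pathology service should hold it, since results go to the requester.

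The cost is modest. Outcomes already come from the hospital's electronic record, and the flag can be added retrospectively to the preintervention data. It must be set before deidentification, because Recruitment has the pathology and elastography teams deidentify their data respectively, and it depends on the person-level linkage that Results describes as ongoing. The counts will be smaller, and diagnoses made at other hospitals will remain unseen; the latter should be stated as a limitation.

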### Study Timeline

#### Preintervention Period

Between August 1, 2023, and January 31, 2024, St Vincent’s Pathology will prospectively collect data on all ALT, AST, and platelet count test results conducted, and APRI and FIB-4 scores will be automatically calculated by the St Vincent’s Pathology data management system, but not reported to the ordering clinician. These data will be prospectively collected from St Vincent’s Pathology by a member of the study team, along with exposure variables outlined above. During the same time period, outcome measures per month will be prospectively collected from the St Vincent’s hospital electronic medical records by a member of the research team (number of FibroScan referrals, number [proportion] of scheduled FibroScan appointments attended, number [proportion] diagnosed with cirrhosis, and number [proportion] linked to specialist care).

#### Intervention Period

From February 1, 2024, to July 31, 2024, St Vincent’s Pathology will commence inclusion of automatic calculation of APRI and FIB-4 score reporting on all pathology blood testing events where an AST, ALT, and platelet count are ordered. St Vincent’s Pathology will provide for these testing events: (1) the APRI result, (2) the FIB-4 result, (3) an explanation of what APRI and FIB-4 measure and what cutoffs are used to define cirrhosis, and (4) recommendations for further investigation of elevated APRI or FIB-4 with transient elastography (FibroScan) and performance of a liver disease screen if underlying liver disease is not known. In addition, a web link to the St Vincent’s Pathology website for liver disease and cirrhosis information page will be included on all blood test reports where APRI and FIB-4 are calculated, with a provided URL link to a unique St Vincent’s Hospital FibroScan referral form. This link will be distinct from the standard fax-based St Vincent’s FibroScan referral form to allow measurement of referrals specifically generated in response to St Vincent’s Pathology APRI or FIB-4 score calculations during the study period.

### Statistical Analysis Plan

#### Outcome Measures

Data will be analyzed per test event and per individual tested.

Primary outcomes of this study include the number of APRI and FIB-4 scores calculated on blood test events conducted during the study period, overall and per month; the number (proportion) of APRI scores that are greater than 1.0 and FIB-4 scores that are greater than 2.67; number of FibroScan referrals overall and per month, operationalized as number of completed FibroScan referrals generated online using the recommended St Vincent’s Pathology FibroScan referral link on the request slip, or St Vincent’s Pathology APRI or FIB-4 calculation web page referral form link; number of individuals with an APRI greater than 1.0 or FIB-4 score greater than 2.67 who undergo a FibroScan test at St Vincent’s Hospital Melbourne overall and per month; proportion of individuals with an APRI greater than 1.0 or FIB-4 score greater than 2.67 who undergo a FibroScan test at St Vincent’s Hospital Melbourne; the number of individuals per month who undergo FibroScan at St Vincent’s Hospital Melbourne who have cirrhosis diagnosed (liver stiffness measurement >12.5kPa); the number (proportion) of individuals with an APRI greater than 1.0 or FIB-4 score greater than 2.67 who have cirrhosis confirmed by FibroScan; the number (proportion) of individuals with etiology-specific cirrhosis range FibroScan results that are referred to the specialist liver clinic; and the number (proportion) of individuals with etiology-specific cirrhosis range FibroScan results that attend to the specialist liver clinic appointment.

The secondary outcomes of this study include the number (proportion) of individuals, stratified by age category, sex, and postcode who have elevated APRI greater than 1.0 and FIB-4 score greater than 2.67, attend the FibroScan clinic for further testing, have etiology-specific cirrhosis range FibroScan scores (kPa), and attend a liver specialist clinic appointment.

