### Objectives

The primary objectives of this study are given below.

First, this study aims to measure the monthly rate and the number (proportion) of individuals with APRI greater than 1.0 and FIB-4 greater than 2.67 among people who undergo automated APRI and FIB-4 calculation on blood test events performed through a single Australian pathology service.

Second, this study aims to measure the monthly rate of transient elastography referrals received after the introduction of automated APRI and FIB-4 reporting, compared with the preintervention period.

Third, this study aims to measure the monthly rate and the number (proportion) of transient elastography tests performed in those with an elevated APRI and or FIB-4 score during the intervention period, compared with the preintervention period.

Fourth, this study aims to measure the monthly rate and the number (proportion) of individuals with APRI greater than 1.0 or FIB-4 greater than 2.67 that have cirrhosis range median stiffness (kPa) confirmed on FibroScan.

Finally, this study aims to measure the number (proportion) of individuals with cirrhosis range FibroScan during the intervention period that is linked to specialist care, compared with the preintervention period.

The secondary objective of this study is to describe the sociodemographic factors associated with (1) APRI greater than 1.0 and FIB-4 greater than 2.67, (2) attendance at FibroScan appointment, (3) cirrhosis diagnosed on FibroScan, and (4) linkage to specialist care.

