### Analysis Methods

The number of APRI and FIB-4 scores generated and the proportion of APRI and FIB-4 scores in the cirrhosis range will be described overall and rates per month will be calculated.

The number (proportion) of individuals with an elevated APRI or FIB-4 who are referred for a FibroScan will be described overall and per month; and the number of FibroScan referrals after the intervention will be compared with the number of FibroScan referrals prior to the intervention by logistic regression modeling (time series analysis with the timepoint of interruption defined as February 1, 2024, when the reported APRI score intervention was introduced).

Similarly, the number (proportion) of individuals with an elevated APRI or FIB-4 who are referred for a FibroScan and who attend their FibroScan appointment, overall and per month, will be described and compared with the number (proportion) of FibroScan appointments attended prior to intervention using linear regression modeling, as well as the number (proportion) of individuals with FibroScan results in cirrhosis range that are referred and attend specialist liver clinic appointments.

The number and proportion of individuals with an elevated APRI or FIB-4 who had cirrhosis confirmed by FibroScan will be described, and sensitivity, specificity, and positive and negative predictive values of APRI for cirrhosis determined by confusion matrix. The area under the receiver operating characteristic curve of APRI and FIB-4 for cirrhosis diagnosis will also be calculated by receiver operating characteristic analysis.

The bivariate distribution of sociodemographic (sex, age category, and urban or regional place of residence [defined by postcode using SEIS data]) and clinical variables (liver disease indication) within the proportion of people with elevated APRI and FIB-4 score, who attend FibroScan testing, have elevated FibroScan results, and attend the liver specialist clinic will be determined and compared with their counterparts using chi-square test for categorical data, 2-tailed Student *t* test for parametric continuous data, and Wilcoxon rank-sum test for nonparametric continuous data as appropriate.

A 2-tailed *P* value of .05 will be used as the significance threshold for all analyses. All analyses will be performed using STATA (version 17; Stata Corporation).

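### The primary referral outcome counts only referrals made through the new web link, so it cannot support the planned before-after comparison of FibroScan referrals

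*Protocol article*

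**What the plan says.** All references are to the protocol article.

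- **Outcome Measures** (under Statistical Analysis Plan) lists the number of FibroScan referrals, overall and per month, as a primary outcome, "operationalized as number of completed FibroScan referrals generated online using the recommended" pathology link, or the form link on the score web page. The article gives no other operational definition of a referral.
- **Comparator Group (Standard of Care)** describes the route before the intervention: "FibroScans are requested through a paper-based referral form by general practitioners or specialists, which is then faxed to the hospital". It describes no web route.
- **Intervention Period** introduces the web form as part of the package from 1 February 2024. It is "distinct from the standard fax-based" form, and it is kept separate "to allow measurement of referrals specifically generated in response to" the reported scores.
- **Objectives** (second primary objective) sets out to measure the "monthly rate of transient elastography referrals received after the introduction of automated APRI and FIB-4 reporting, compared with the preintervention period".
- **Analysis Methods** has the number of referrals after the intervention "compared with the number of FibroScan referrals prior to the intervention by logistic regression modeling", with the interruption at 1 February 2024.
- **Preintervention Period** says that monthly outcome counts come from "hospital electronic medical records by a member of the research team (number of FibroScan referrals" heads the list). It does not name the channel.
- **Sample Size Justification** claims power for a 10% difference in referral rates before and after. It gives no baseline rate.

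**The concern.** A before-after comparison needs an outcome that can occur, and is counted in the same way, in both periods. Here the counted event is use of a form that opens on the date of the interruption. A patient who would have been referred by fax in any case, and is now referred on the web, counts as an effect. A patient referred by fax because a reported score prompted it does not count at all. The outcome therefore measures uptake of a channel, whereas the objective asks whether more people are referred.

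Referral is a named primary objective, comes first among the effects listed in the abstract's objective, and has its own power statement. A misleading result here would weigh on the trial's conclusion about whether automated reporting changes practice.

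**Working it through.** **The plan's own figures.** The 10% difference in referral rates cannot be reproduced, because no baseline rate, power or number is given for it. The 1100 per subgroup stated for a 5% difference in proportions with 90% power also lacks a baseline. With the pooled two-proportion formula and two-sided 0.05 it is reached only by assuming, for example, 13% versus 18% (1099). That figure has no bearing on what follows. The 10% claim matters in one respect: a relative difference from a baseline of zero is undefined, so the claim presupposes a non-zero preintervention count.

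**Inputs from the article.** Two periods of six months (August 2023 to January 2024; February to July 2024), two-sided 0.05, fax route before, web link added at the interruption. **Assumed, because the article gives no referral counts:** total referrals F per six months, unchanged by the intervention, and a share s that moves from fax to web.

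**Reading A: the web-only definition in both periods.** Before = 0 and after = sF. With equal periods and Poisson counts, given k referrals in total, the number before is binomial(k, 0.5) under no change. For 0 versus k the exact two-sided p is 2 × 0.5^k:

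- k = 5: 2 × 0.03125 = 0.0625
- k = 6: 2 × 0.015625 = 0.031

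So six web referrals in six months, one a month, cross the threshold with no true change. Examples:

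| F | s | Web-only, before vs after | p | All routes, before vs after |
|---|---|---|---|---|
| 60 | 5% | 0 vs 3 | 0.25 | 60 vs 60 |
| 60 | 10% | 0 vs 6 | 0.031 | 60 vs 60 |
| 150 | 10% | 0 vs 15 | 0.00006 | 150 vs 150 |
| 300 | 25% | 0 vs 75 | < 10^-20 | 300 vs 300 |

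This simple test stands in for the planned regression. In the planned logistic model, a preintervention count of exactly zero leaves the period coefficient without a finite maximum-likelihood estimate.

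**January 2024.** The Intervention section places the notice to clinicians, including a website banner linking to further information, about one month before the start, and it lists the referral form among the website content. The form may therefore have been live in the last preintervention month. If one web referral arrived then, p for 1 versus k is 2 × (1 + n) × 0.5^n with n = k + 1. For 1 versus 7 (n = 8) this is 2 × 9/256 = 0.070; for 1 versus 8 (n = 9) it is 2 × 10/512 = 0.039. The threshold moves a little and the problem stays.

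**Reading B: all hospital-record referrals before, web-only after.** Apparent change = (sF − F)/F = s − 1. For s = 5%, 10%, 25% and 50% this is −95%, −90%, −75% and −50%, again with no true change.

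**Reading C: all routes in both periods.** Apparent change = (F − F)/F = 0%, which is correct.

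**The case against.** The strongest reply is that the authors did not intend a baseline of zero. Preintervention referrals are taken monthly from hospital records, which at that time would hold fax referrals. The second objective speaks of referrals received, without naming a channel. A 10% difference in rates makes sense only with a real baseline. This stands as evidence of intent, and it is why a fixed direction of bias cannot be claimed. It does not rescue the plan, because the web-only definition is still the one written down; if it then applies only after 1 February, the result is Reading B.

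A second reply is that the separate link serves attribution. That is sound: a count of link referrals is a useful process measure within the intervention phase. The fault lies only in using it as the outcome of a before-after test.

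A third is that referral is one of several primary outcomes. FibroScans undergone by people with an elevated score, cirrhosis diagnosed, and referral to and attendance at the liver clinic are not defined by the link, and pure substitution of web for fax would not by itself change them. This stands and limits the damage.

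A reader might infer more than the article supports: that an increase is guaranteed, that any use of the link would be significant, or that the preintervention count is zero in all six months. The first holds only under Reading A. The second is wrong even there, since 0 versus 5 gives p = 0.0625. The third is a strong inference for five months but is unsettled for January 2024.

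**Conclusion.** The referral outcome as defined cannot support the comparison in the Objectives and Analysis Methods, or the 10% difference in the Sample Size Justification. This rests on the text alone. The direction of the error depends on how the conflict is resolved. With the definition applied to both periods, an increase appears without any change in total referrals, and about six web referrals in six months suffice for significance. With hospital-record counts before and web-only counts after, the bias is towards a decrease, from −95% to −50% in the illustrations.

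The sizes rest on assumed totals, assumed shares moving to the web, unchanged total referrals and, for the p-values, Poisson counts over equal periods. The invalidity of the comparison does not depend on them. It should be corrected before the analysis, which the article expects to begin in August 2024. The other primary outcomes are not affected by this point.

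**What to change.** In Outcome Measures, define the compared outcome identically in both periods: all completed FibroScan referrals received by the hospital service by any route, fax plus web. Use the monthly hospital-record counts described for the preintervention period and continue them through 31 July 2024. Where the planned linkage allows, give the same count among individuals with an elevated APRI or FIB-4.

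Report web-link referrals as a descriptive uptake measure for the intervention phase, without a before-after test, and tabulate fax and web separately by month so that substitution is visible. State whether the web form was live in January 2024.

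A split by community requester would sharpen the comparison, since specialists also use the fax form. Requester type is not among the listed variables, so the split should be made only if the referral records hold it.

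Cost: for the total count, a change of wording plus counting fax referrals in both periods. The count among people with an elevated score depends on linkage that the Results section describes as still under way. The observed effect may be smaller than with web-only counting.
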